### Interventions

All subjects will receive the registered oral cholera vaccine Dukoral^®^ according to the standard vaccination scheme on visit 2 and visit 5 (2 doses, 14 days apart). Participants will take probiotic lysate material or a placebo for 6 weeks (day 1–43). Both products will be coated with identical colors and shapes and will be provided to the subjects in bottles. A daily serving consists of two chewable tablets, to be taken as one tablet twice a day.

### Outcome measures

Outcomes related to efficacy and safety will be evaluated. Trained investigators and research coordinators will conduct interviews and blood sampling of subjects. Participants will be instructed to visit after a 12-hour overnight fast on each visit. The vaccination time points are fixed on day 15 and day 29. On the day of taking the vaccine, blood must be collected before providing the vaccine. Fecal samples will be collected on days 0, 14, 16, 17, 28, 30, 31, and 42 at the subjects’ homes. Fecal sampling will be allowed on day 1 or day 43, respectively, when it is difficult to collect samples on day 0 or day 42. If subjects cannot collect a fecal sample on day 0 or day 1, they will collect a fecal sample as soon as possible and start intake of the study product the day after collecting the first fecal sample. The stool sample is frozen in the home freezer and can be submitted with ice packs the next day or delivered to the laboratory within an hour through the delivery system provided.

### Efficacy variables

To assess local inflammatory response, calprotectin and beta-defensin levels will be analyzed in feces at visits 1–7. At visits 2, 5, and 7, cholera toxin-specific Immunoglobulin A (IgA) and Immunoglobulin G (IgG) levels in plasma will be confirmed. Intestinal fatty-acid binding protein (I-FABP) as an intestinal epithelial damage/repair marker, cytokines/chemokines (Interferon gamma-induced protein 10 (IP-10), etc.), acute-phase proteins such as high-sensitivity CRP and Interleukin 1 receptor antagonist (IL-1ra) in plasma will be analyzed to further explore the systemic inflammatory response on visit 2–7. Blood cellular markers (leukocytes, lymphocytes, neutrophils, etc.) will be monitored at every visit. Analyses for the gut microbiome will be performed on visits 1, 2, and 7. Bristol stool scale questionnaire will be conducted by online survey every day.

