## Abstract

It is crucial for human health that the immune system of the gastrointestinal tract works effectively. Dietary modulation is one of the factors that regulate the immune response in the gut. This study aims to develop a safe human challenge model to study gastrointestinal inflammation and immune function. This study focuses on evaluating gut stimulation induced by the oral cholera vaccine in healthy people. In addition, this paper describes the study design for assessing the efficacy and safety of a probiotic lysate, identifying whether functional ingredients in food can modulate inflammatory response induced by oral cholera vaccine. Forty-six males aged 20 to 50 with healthy bowel habits will be randomly allocated to the placebo or intervention group. Participants will consume 1 capsule of probiotic lysate or placebo twice daily for 6 weeks, take oral cholera vaccines on visit 2 (day 15) and visit 5 (day 29). The level of fecal calprotectin, a marker of gut inflammation, will be the primary outcome. The changes of cholera toxin-specific antibody levels and local/systemic inflammatory responses will be evaluated in blood. The purpose of this study is to evaluate gut stimulation of the oral cholera vaccine and investigate the effect of a probiotic lysate on improving the mild inflammatory response induced by the vaccine or supporting the immune response in healthy subjects.

**Trial registration**: * This trial is registered in the International Clinical Trials Registry Platform of WHO (ICTRP, registration number: KCT0002589).

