### Safety variables

Blood chemistry and vital signs will be monitored at every visit. Aspartate Aminotransferase (AST) and Alanine Aminotransferase (ALT) will be measured on days 0 and 43. Vital signs (body temperature, systolic/diastolic blood pressure, and pulse rate) will be confirmed at every visit. Unusual signs will be monitored by online questionnaires during the study. Unintended changes in pathological, anatomical, metabolic, or physiological functions associated with the use of a study product are considered side effects, except for changes associated with normal activities that are ordinarily clinically expected to change in frequency or magnitude form. The PI will assess all AEs as to their severity and relation to the study product. Appropriate treatment and follow-up will be performed, which will continue until the condition is resolved or the cause is identified.

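### CRP and the other plasma inflammation markers have a pre-vaccine value at visit 2 but no value from before the product starts

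*Protocol article*

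**What the plan says.** All references are to the protocol article.

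- **Marker schedule (Efficacy variables).** I-FABP, cytokines and chemokines such as IP-10, hsCRP and IL-1ra "in plasma will be analyzed to further explore the systemic inflammatory response on visit 2–7". Visit 1 is not included.
- **Product (Interventions).** "Participants will take probiotic lysate material or a placebo for 6 weeks (day 1–43").
- **Vaccine (Abstract).** Participants "take oral cholera vaccines on visit 2 (day 15) and visit 5 (day 29").
- **Order on vaccine days (Outcome measures).** "On the day of taking the vaccine, blood must be collected before providing the vaccine".
- **Blood at the other visits.** "Blood cellular markers (leukocytes, lymphocytes, neutrophils, etc.) will be monitored at every visit" (Efficacy variables). "Blood chemistry and vital signs will be monitored at every visit", and "Alanine Aminotransferase (ALT) will be measured on days 0 and 43" together with AST (Safety variables).
- **Fecal markers.** Calprotectin and beta-defensin run from visit 1. The first stool sample is due on day 0, with day 1 allowed. If it is later than that, product start is postponed until the day after the sample (Outcome measures).
- **Analysis (Statistical analysis).** A linear mixed model with group and time as fixed effects and subject as random effect contrasts the arms' changes across the whole period on product.

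**The concern.** The trial asks two questions: does the vaccine provoke a mild inflammatory response, and does the lysate modify it? The first needs a value from just before the vaccine, and visit 2 supplies it. For the second, visit 2 lies 14 days after product start, so the lysate may already have altered it.

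The planned comparison covers the whole period on product, yet for these markers days 1 to 15 are not observed. Any change score has to start from a value measured on product. The fecal markers are handled differently: the protocol even delays product start to secure their first sample. CRP is one of the two outcomes in the sample size section, so a reader will look at the lysate effect on it.

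At stake are the meaning of a change over the intervention period for these markers, some precision in a small trial, and the ability to see whether the arms differed by chance before product. An analysis plan written later cannot restore a value that was never measured.

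**Working it through.** **Timing.** First plasma value: day 15. Product start: day 1. 15 − 1 = 14 days on product. Blood on day 15 is taken before the vaccine, so visit 2 is pre-vaccine and post-product.

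**What a change from visit 2 estimates.** Let the lysate-minus-placebo effect be *e* at visit 2 and *L* at a later visit. Comparing later levels estimates *L*. Comparing changes from visit 2 estimates *L* − *e*. If *L* = *e*, the change score shows no effect. If *e* is negative and *L* is zero, it shows a larger rise after vaccination on lysate. A change from a pre-product value would estimate *L*.

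**The plan's CRP sample size.** Inputs (Sample size calculation): 2.54 ± 2.07 against 1.01 ± 0.88 mg/L, two-sided α 0.05, 80% power, paired, stated n = 18.
- Difference: 2.54 − 1.01 = 1.53.
- SD of the paired difference at correlation 0 (the correlation is not stated): √(2.07² + 0.88²) = 2.249.
- n = ((1.960 + 0.842) × 2.249 / 1.53)² = 16.96, so 17. The t-based version gives 19 at correlation 0 and 18 at correlation 0.1.

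The stated 18 is reproduced closely. It rests on a before-after contrast within the placebo group, which visit 2 serves fully.

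**Completers.** 23 × 0.8 = 18.4, so about 18 per group.

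**Chance imbalance before product.** With SD 0.88 and 18 per group, the standard error of the difference is 0.88 × √(2/18) = 0.293. The 95% range is 1.96 × 0.293, about ±0.57 mg/L.

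**Precision from a pre-product covariate.** The correlation *r* with later values is an assumption. Residual variance is 1 − r², and the equivalent sample size multiple is 1/(1 − r²). The detectable difference at 80% power, taking SD 2.07 in both arms as an assumption, is (1.960 + 0.842) × 2.07 × √(2/18) × √(1 − r²).

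| r | residual variance | n multiple | detectable CRP difference, mg/L |
|---|---|---|---|
| no baseline | 1.00 | 1.00 | 1.93 |
| 0.3 | 0.91 | 1.10 | 1.84 |
| 0.5 | 0.75 | 1.33 | 1.67 |
| 0.7 | 0.51 | 1.96 | 1.38 |

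**Gain over a model that already conditions on visit 2.** Assume the same correlation *r* between visit 1, visit 2 and the later value. Residual variance with both covariates is 1 − 2r²/(1 + r).
- r = 0.5: 1 − 0.50/1.5 = 0.667, against 0.75 with visit 2 alone; 0.667/0.75 = 0.89.
- r = 0.7: 1 − 0.98/1.7 = 0.424, against 0.51; 0.424/0.51 = 0.83.

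The further reduction is 11% to 17%, not 25% to 49%. The model with visit 2 as covariate also answers a different question, because it conditions away early lysate effects.

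**The case against.** The strongest defence is that two weeks of product followed by a challenge is the design. The hypothesis in the Discussion concerns the response provoked by the vaccine, not resting inflammation. For that question the value just before the vaccine is the natural reference, and *L* − *e* may be just what is wanted. This stands, and visit 2 should keep that role. It does not supply a reference for change over the whole period on product, which the Statistical analysis section also sets out to compare.

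The markers are described as further exploration, and the primary outcome, fecal calprotectin, has a pre-product sample. This stands and limits the weight of the point.

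A reader might infer more than the document supports:

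- *That the lysate comparison is invalid.* It is not. Levels from visit 2 onward can be compared between randomised arms without a baseline.
- *That a group difference at visit 2 cannot be told from chance.* A between-group test at visit 2 measures the difference against chance. What is missing is a way to see or adjust for imbalance that was there before product.
- *That the CRP sample size is undermined.* It rests on the within-placebo rise, for which visit 2 is the right baseline.
- *That the plan will subtract visit 2.* The article does not say so for these markers; its mixed model is not specified to that level.
- *That 1.3 to 2.0 times the sample size is being lost.* That multiple assumes r between 0.5 and 0.7 and compares with an analysis that uses no earlier value.
- *That even a complete suppression of the CRP rise would go undetected, because 1.93 exceeds 1.53.* This takes SD 2.07 in both arms. If the rise were abolished, the lysate arm might instead have SD 0.88. The root-mean-square SD is then √((2.07² + 0.88²)/2) = 1.59, and the detectable difference is 2.802 × 1.59 × √(2/18) = 1.49.

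Finally, the schedule figure is not available here, so it cannot be checked whether it lists these markers at visit 1. The text says visits 2 to 7.

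**Conclusion.** The point holds as a limited one. By the text, none of these plasma markers has a value from before the product. As a result, a change over the intervention period cannot be formed for them, a change from visit 2 excludes whatever the lysate did in its first 14 days, and pre-product imbalance (about ±0.57 mg/L for CRP, assuming SD 0.88 and 18 completers per group) stays unseen and unadjusted.

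The loss is in precision and interpretation, not validity. Its size depends on a correlation that the article does not give: residual variance 0.75 at r = 0.5 and 0.51 at r = 0.7 against no baseline, with a smaller gain over a model that uses visit 2. The primary outcome and the stated sample sizes are untouched. It is a weakness of the sampling schedule for exploratory markers, worth correcting because the remedy is cheap and cannot be applied at the analysis stage.

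**What to change.** Assay I-FABP, the cytokines and chemokines, hsCRP and IL-1ra also in blood taken at visit 1, before the first product intake, and change the schedule for these markers to visits 1 to 7. State which value serves which comparison: visit 1 as covariate for lysate against placebo over the intervention period, and visit 2 as the pre-vaccine reference for the vaccine response, including the within-placebo CRP rise.

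The cost is one plasma aliquot per participant and 46 assays per marker, or 4 × 46 = 184 for the four named markers. No visit is added, since blood is already drawn at visit 1 for cell counts and chemistry. The article does not say that plasma is separated or stored at that draw, so this handling step must be confirmed. No stated sample size changes.

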### Safety variables

Blood chemistry and vital signs will be monitored at every visit. Aspartate Aminotransferase (AST) and Alanine Aminotransferase (ALT) will be measured on days 0 and 43. Vital signs (body temperature, systolic/diastolic blood pressure, and pulse rate) will be confirmed at every visit. Unusual signs will be monitored by online questionnaires during the study. Unintended changes in pathological, anatomical, metabolic, or physiological functions associated with the use of a study product are considered side effects, except for changes associated with normal activities that are ordinarily clinically expected to change in frequency or magnitude form. The PI will assess all AEs as to their severity and relation to the study product. Appropriate treatment and follow-up will be performed, which will continue until the condition is resolved or the cause is identified.

### Possible covariables

Age, medical history, and lifestyle (alcohol history and smoking use) will be assessed at baseline. Participants’ current medication history and supplement use will be checked at each visit. Weight will be measured at each visit, and height will be measured on the first visit. Body mass index (BMI) will be calculated using measured weight and height [weight (kg)/height (m^2^)]. The same researcher will use the same equipment to measure parameters for each visit. Subjects will also fill out our recommended food score questionnaire at the beginning and submit their diet diary every week, 2 days on weekdays, and 1 day on weekends using a mobile application during the study for monitoring dietary compliance. Participants will be asked to limit intakes of health functional foods, avoid the consumption of pre-or probiotics products such as dietary fiber, oligosaccharide, etc. In addition, alcohol consumption will not be permitted as well as the day before sampling (days -1 and 0, days 13–17, days 27–31, days 41–43).

### Compliance

Compliance will be assessed biweekly by interviewing subjects and counting the study product returned to the clinic. Consuming less than 80% of the scheduled intakes will be defined as non-compliance. Subjects will be called as appropriate to encourage compliance.

### Data management and quality assurance

All data generated by the methods described in the study protocol will be recorded on the electronic CRFs. Steps taken to assure the reliability and accuracy of the study data include the selection of qualified PIs, research coordinators, research assistants, and contract laboratory; review of protocol procedures with the PIs, protocol writer, and associated personnel before the study; and the presence of a research coordinator during the study days. The research coordinator will review CRFs for accuracy and completeness. The sponsor will carry out periodic on-site monitoring of study procedures and documents.

### Statistical analysis

Data analyses will be performed with intention-to-treat subject data (all data from subjects who have received the study product) or per-protocol subject data (only data from subjects who completed the study at least 80% compliant with the study product). Variables will be tested for normal distribution and data transformation will be performed on skewed variables. Parametric or non-parametric analyses (dependent on the outcome of the distribution of data) such as paired *t*-test, Student’s *t*-test, or Wilcoxon signed-rank test will be used to analyze the difference within each group or between the groups for continuous variables. Chi-square or Fisher’s exact test will be used to analyze the difference between the groups for categorical variables. A linear mixed-effects model with group and time as fixed effects and subject as the random effect will be applied to compare the changes between groups over the intervention period. The correlation between variables will be analyzed by Pearson’s correlation or Spearman correlation and regression analysis will be performed. The data will be analyzed using the SAS 9.4 statistical software. The difference between the groups will be tested two-sided for all study outcomes. *P*-values <0.05 are classified as statistically significant.

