In this study, we describe clinical trials which will evaluate the effect of *Lb*. *plantarum* lysate on the inflammatory response or on the immune response, suggesting the protocol that the oral cholera vaccination can be used as a model to induce a mild inflammatory response in the gut. Oral cholera vaccinations are used to induce an immune response in the intestine to prevent cholera infection. However, oral vaccines can also affect the immune response of other mucosal tissues. Oral vaccination primarily interacts with the immune system through the oral cavity to the small intestine and induces the expression of vaccine-specific IgA in gastrointestinal and tissue-specific homing of B cells and T cells [28]. The aim of the measurement of cholera toxin-specific IgA was to evaluate whether oral cholera vaccination is able to induce potent IgA responses in serum.

We hypothesized first, the oral cholera vaccination will induce a significant increase in the gut inflammatory response in the gastrointestinal tract, and second, *Lb*. *plantarum* K8 lysate will significantly improve the inflammatory response or support the immune response induced by oral cholera vaccination in healthy male subjects. To our knowledge, this is the first randomized, double-blind study to investigate the efficacy of *Lb*. *plantarum* lysate on the inflammatory response as induced by oral cholera vaccination. We expect that the results of this study will contribute to the scientific evidence that the tested probiotic lysate has the potential of modulating intestinal inflammation induced by the oral cholera vaccine or improving the immune response.

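### No lead analysis set is named, and the lysate claim is not tied to the primary calprotectin outcome, so a post-randomisation subset or any one of several unadjusted markers could carry it

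*Protocol article*

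**What the plan says.** **Analysis set** (Statistical analysis): "Data analyses will be performed with intention-to-treat subject data (all data from subjects who have received the study product) or per-protocol subject data". The second set is defined as "only data from subjects who completed the study at least 80% compliant with the study product". Neither is called primary.

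**Testing** (Statistical analysis): "The difference between the groups will be tested two-sided for all study outcomes", and P-"values <0.05 are classified as statistically significant". No order or adjustment across outcomes is stated. The same section lists t-tests and non-parametric tests, and also a mixed model with group, time and a random subject effect.

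**Hypothesis** (Discussion): the lysate "will significantly improve the inflammatory response or support the immune response induced by oral cholera vaccination". The last sentences of the Abstract and of the Discussion repeat the same alternative.

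**Primary outcome** (Abstract): "The level of fecal calprotectin, a marker of gut inflammation, will be the primary outcome". No time point or contrast is attached.

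**Markers** (Efficacy variables): "calprotectin and beta-defensin levels will be analyzed in feces at visits 1–7". The section also names cholera toxin-specific IgA and IgG, I-FABP, IP-10, hsCRP and IL-1ra. That makes eight named markers, and the list of cytokines is left open.

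**Compliance and removal**: the Compliance section sets the threshold at 80% of scheduled intakes. Handling of withdrawal permits, but does not require, removal of a subject for compliance reasons.

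**The concern.** Two choices that decide what the trial concludes are written as alternatives: which subjects are analysed, and which kind of response counts as benefit.

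The first is mainly a matter of bias. Completion and intake are observed after randomisation and may depend on tolerance of the product or on the response to the vaccine. A main result from the per-protocol set is therefore no longer a comparison of the groups as randomised.

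The second is a matter of false positives. If a significant result on any inflammatory or antibody marker can be read as support for the hypothesis, a lysate with no effect has several chances to succeed, each at the full 0.05. The Discussion also argues that no single marker can capture the intestinal immune response, which suggests that conclusions will draw on several.

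At stake is whether a positive lysate finding from 46 subjects could be taken as evidence of efficacy.

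**Working it through.** The article states no overall error rate, so there is no such figure to reproduce. Its only error rate for the analysis is 0.05 per two-sided test.

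**Inputs from the article**
- Level 0.05, two-sided, every outcome (Statistical analysis).
- Eight named markers (Efficacy variables): calprotectin, beta-defensin, IgA, IgG, I-FABP, IP-10, hsCRP, IL-1ra.
- 23 per group with 20% drop-out (Sample size calculation).
- Faecal samples on days 0, 14, 16, 17, 28, 30, 31 and 42 (Outcome measures), so seven after day 0.

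**Assumptions**
- No true effect on any marker, and one test per marker.
- Pairwise correlation between markers is not given, so 0 to 0.5 is shown.

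**Step 1. Size of the per-protocol set.** 23 × 0.8 = 18.4, so about 18 per group if the planned drop-out occurs. Low compliance would reduce it further.

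**Step 2. Eight markers, one analysis set.**
- Either direction, independent: 1 − 0.95^8 = 33.7%. Simulated at correlation 0.5: about 25%.
- Favouring the lysate only (0.025 per test), independent: 1 − 0.975^8 = 18.3%. Simulated at correlation 0.5: about 12–13%.

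**Step 3. What the choice of set adds.** Simulation under no effect with 23 per arm, t-tests, and a per-protocol set made of a random 18 of 23 in each arm. A result counts if it is significant in either set.

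| Outcomes tested | One set, two-sided | Either set, two-sided | Either set, favouring lysate |
|---|---|---|---|
| 1 | 5% | about 7% | about 4% |
| 2 (one inflammatory, one immune) | 9–10% | 13–14% | about 7% |
| 8 | 25–34% | 34–45% | 17–25% |

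For one outcome, the either-set figure runs from 5.9% with 5% of subjects excluded to 7.6% with 30% excluded. Exclusion was random in this simulation, so these figures contain no selection bias. The size of that bias cannot be derived from the article.

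**Step 4. Calprotectin alone, as an upper scenario.** If each of the seven later samples were tested separately, 1 − 0.95^7 = 30.2% if independent and about 23% at correlation 0.5. Favouring the lysate: 1 − 0.975^7 = 16.2%, and about 11%.

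**The case against.** The strongest reply is that this is a condensed article and that an analysis plan usually names the lead set, the primary contrast and any multiplicity rule. That holds for the contrast, whose absence alone would not be a finding. It does not dispose of the rest, because the article does more than stay silent: it states alternatives for both the analysis set and the hypothesis. If the first alternative only means that both sets will be reported, there is still no rule for when they disagree.

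Several further points limit the concern.
- Calprotectin is named as primary. If the lysate conclusion were tied to it, most of the inflation would go.
- The markers are not equal routes to a claim. The systemic markers are described as exploration, and IgA as a check that the vaccine raises an antibody response.
- The planned mixed model compares the groups over the whole period, so seven separate calprotectin tests are an upper scenario. The day 14 sample also precedes the first vaccine dose on day 15 and cannot show a modulated vaccine response.
- The product code stays closed until the data have been analysed. This limits deliberate selection in the lysate's favour, but does not settle which result counts once the code is open.

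A reader might infer that a false lysate claim is likely, or that it has a 34% chance. The figures do not support this. The 34% counts results in both directions; the part favouring the lysate is about half of it. Even with 16 tests (an assumption of two post-vaccination windows per marker) and either set allowed, it reaches only 25–44%.

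A reader might also infer that the article lays down a formal rule by which any one significant marker proves efficacy, or that intake below 80% triggers removal. It does neither. The hypothesis is narrative text in the Discussion, and removal is permissive.

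**Conclusion.** The point holds in a limited form. The article leaves the lead set open between one close to intention-to-treat and one selected after randomisation, and it does not tie the lysate claim to the outcome it calls primary.

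The chance of a spurious significant result is well above nominal: for eight markers on one set, 25–34% in either direction, and about 12–18% favouring the lysate against 2.5%. Most of this comes from the number of outcomes. The choice of set adds about 2 points for a single outcome and matters chiefly because of bias. These figures assume one test per marker, no true effect and correlations between 0 and 0.5.

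The trial can run as designed, but a positive lysate claim made under this wording would be hard to interpret. The point about removal of non-compliant subjects is secondary.

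**What to change.** 1. Name all randomised subjects who took product as the lead set, and per-protocol as a sensitivity analysis.
2. Base the lysate claim on one pre-stated between-group calprotectin contrast from samples already scheduled, at two-sided 0.05. One option, from the planned mixed model, is log calprotectin over days 16, 17, 30 and 31 (one and two days after each vaccine dose), adjusted for day 0. Another single contrast fixed in advance would also serve.
3. Label all other markers, antibodies included, as secondary or exploratory and not grounds for an efficacy claim on their own.
4. Where a subject is non-compliant with product but still consents, and there is no safety reason to stop, keep collecting the scheduled samples so that the lead set is complete. This concerns data collection only.

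**Effect:** with one set and one contrast fixed, the type I error for the lysate claim is 5%.

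**Cost:** items 1 to 3 are wording. Item 4 adds slight sampling follow-up. A positive antibody or secondary-marker result could no longer be presented as proof of efficacy. The sample size section works from paired testing, so its stated power does not carry over to a between-group contrast and should not be quoted for it.

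### The named lysate-versus-placebo analyses of calprotectin do not adjust for the day-0 stool value that the trial already collects, so the comparison is valid but less precise than it could be

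*Protocol article*

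**What the plan says.** All places are in the protocol article.

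- **Primary outcome (Abstract):** "The level of fecal calprotectin, a marker of gut inflammation, will be the primary outcome".
- **Sampling (Outcome measures):** "Fecal samples will be collected on days 0, 14, 16, 17, 28, 30, 31, and 42 at the subjects’ homes". This gives one stool at the start and seven later ones. A late first stool delays the product: "they will collect a fecal sample as soon as possible and start intake of the study product the day after collecting the first fecal sample". There is also a window: "Fecal sampling will be allowed on day 1 or day 43, respectively, when it is difficult to collect samples on day 0 or day 42".
- **Assays (Efficacy variables):** "calprotectin and beta-defensin levels will be analyzed in feces at visits 1–7".
- **Tests (Statistical analysis):** for continuous variables, methods "such as paired *t*-test, Student’s *t*-test, or Wilcoxon signed-rank test will be used to analyze the difference within each group or between the groups".
- **Longitudinal model (Statistical analysis):** "A linear mixed-effects model with group and time as fixed effects and subject as the random effect will be applied". Its stated purpose is to compare changes between the groups over the intervention period.

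The same section also mentions a regression analysis, in the sentence on correlations, without naming an outcome or covariates. The section on possible covariables lists age, history, lifestyle, medication, supplements, body size and diet. It does not list baseline calprotectin and ties none of its items to a model.

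**The concern.** The second hypothesis, that the lysate modifies the vaccine-induced response, rests on the randomised comparison of two small groups: 23 men each, or 19 after the planned losses. The sample size was derived for a paired, within-group test, so the article gives no power for this between-group comparison.

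In that setting a pre-treatment measurement of the primary outcome is usually the most useful covariate available. Here it is collected but is not named as a covariate. The t-test can be applied to levels, which leaves day 0 unused, or to changes, which subtracts the whole day-0 value whatever its correlation with later values. In the mixed model as named, day 0 can enter only as one more response. The price is a wider confidence interval for the lysate effect and lower power.

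**Working it through.** **The plan's own figure.** Sample size calculation gives 19 per group for calprotectin: mean 15, SD 20, rise to 50 μg/g, two-sided paired test, alpha 0.05, power 90%. With n = ((1.960 + 1.282) × SD / difference)²:

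- difference 35, SD 20: 3.4, so 4;
- difference 35, SD of differences 28.3: 6.9, so 7;
- difference 15, SD 20: 18.7, so 19.

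The stated 19 therefore does not follow from a shift of 15 to 50. That is a separate matter. What counts here is that the calculation is within-group and supplies neither a between-group effect nor a within-man correlation.

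**Inputs.** From the plan: SD 20 μg/g, 19 and 23 per group, two-sided 0.05. Assumed: a 15 μg/g lysate-placebo difference, and rho between day 0 and a later stool of 0.5 (range 0.3 to 0.7), with equal SD at both times.

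**SD of the analysed quantity, one later stool.**

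- Level: 20.
- Change from day 0: 20 × √(2(1 - rho)), which is 23.7, 20.0 and 15.5 at rho 0.3, 0.5 and 0.7.
- Adjusted for day 0: 20 × √(1 - rho²), which is 19.1, 17.3 and 14.3.

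**Variance ratios.** Adjusted to level is 1 - rho² = 0.91, 0.75, 0.51. Adjusted to change is (1 - rho²)/(2(1 - rho)) = (1 + rho)/2 = 0.65, 0.75, 0.85. The second is below 1 for every rho below 1.

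**Power.** Noncentral t with noncentrality 15 / (SD × √(2/n)) and 2n - 2 degrees of freedom, one fewer with the covariate. Example at n = 19, rho = 0.5: unadjusted 15 / (20 × 0.3244) = 2.31 on 36 df, power 61.4%; adjusted 15 / (17.32 × 0.3244) = 2.67 on 35 df, power 73.7%.

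| n per group | rho | Levels | Changes | Adjusted | Gain over levels | Gain over changes |
|---|---|---|---|---|---|---|
| 19 | 0.3 | 61.4% | 47.7% | 65.4% | 4.0 | 17.7 |
| 19 | 0.5 | 61.4% | 61.4% | 73.7% | 12.3 | 12.3 |
| 19 | 0.7 | 61.4% | 82.7% | 88.2% | 26.8 | 5.5 |
| 23 | 0.3 | 70.1% | 55.7% | 74.1% | 4.0 | 18.4 |
| 23 | 0.5 | 70.1% | 70.1% | 81.9% | 11.8 | 11.8 |
| 23 | 0.7 | 70.1% | 89.5% | 93.6% | 23.5 | 4.1 |

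Gains are in percentage points. Estimating the covariate's slope adds about 3% to the variance with 38 men (1 + 1/34 = 1.029). Charging this lowers the adjusted power at rho 0.5 only to 72.5% (n = 19) and 81.0% (n = 23).

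**Other effect sizes, n = 19, rho = 0.5.** At 10 μg/g, power goes from 32% to 41%. At 25 μg/g it goes from 96% to 99%. At 35 μg/g all three methods exceed 99%.

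**Repeated stools.** A random subject effect alone implies equal correlation rho between any two stools. For the mean of the seven later stools, the variance in units of SD² is:

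- levels: rho + (1 - rho)/7;
- changes: (1 - rho)(1 + 1/7);
- adjusted: the levels figure minus rho².

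At rho 0.5 these are 0.571, 0.571 and 0.321, a ratio of 0.56 against either. At rho 0.3 and 0.7 the ratios are 0.775 and 0.34 against levels, and 0.39 and 0.74 against changes. A mixed model with day 0 as a response and an added group-by-time term estimates the raw change contrast, so the term alone does not recover the loss.

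**The case against.** The strongest reply is that this concerns efficiency and is not an error. Allocation is randomised, so an unadjusted comparison of levels or of changes is unbiased and keeps its type I error. That stands. A reader might infer that the planned tests are invalid or biased; nothing in the article supports this.

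Other readings also go too far:

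- **That the listed analyses are exhaustive.** The tests are given as examples and an unspecified regression is added, so a fuller plan could contain adjustment. The point survives because the article names the mixed model's fixed effects and baseline is not among them.
- **That baseline is ignored.** The mixed model is meant to compare changes, and day 0 may enter it as a response. For that model the fair comparator is change, where the gain at rho 0.7 is 5.5 points (n = 19) or 4.1 (n = 23), not the 27 or so points over levels.
- **That chance imbalance is likely because the SD exceeds the mean.** In SD units, the standard error of a day-0 group difference is √(2/19) = 0.32 whatever the mean. It depends on group size only.
- **That every man has a value from before product.** A day-1 stool is allowed and product is taken from day 1, so such a stool may follow the first intake.

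Finally, rho and the 15 μg/g effect are not in the documents. This limits what can be said about the size of the gain. It does not affect its direction against raw change, apart from the small cost of estimating the slope when rho is close to 1.

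**Conclusion.** The point holds as a matter of precision. The named between-group analyses of the primary outcome leave out a covariate that the trial already collects. Under SD 20 and an assumed 15 μg/g difference, power at rho 0.5 rises by about 12 points at either group size. Over assumed rho of 0.3 to 0.7 and both group sizes, the gain is about 4 to 27 points over levels and about 4 to 18 over changes. It is modest over levels when rho is low and over changes when rho is high, and it nearly vanishes for effects of 25 μg/g or more at rho 0.5. The power figures are for one later stool on the raw scale. If calprotectin is transformed for skewness, as the plan allows, the same variance ratios apply with rho taken on the transformed scale. The change should be made because it is nearly free and the between-group comparison has no stated power to spare.

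**What to change.** In Statistical analysis, state that the lysate-versus-placebo comparison of calprotectin uses the stools after day 0 as responses. The baseline value, transformed in the same way as the outcome (for example, log), enters as a covariate, with group, time and group-by-time as fixed effects and subject as random effect. At any single time point, use ANCOVA in place of the t-test. Apply the same rule to beta-defensin, which is measured in feces at the same visits.

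Define the covariate as the first (day-0) stool and not the day-14 stool: day 14 follows two weeks of product, and adjusting for it could remove part of the lysate effect. Where a day-1 stool stands in for day 0, record whether it preceded the first intake.

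The cost is one or two sentences and one degree of freedom, with no new samples, visits or participants.
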